### Process Evaluation

An evaluation of the use of mobile phones to promote breastfeeding practices was conducted with participants from the intervention group. Information on text delivery success, user experiences (user-friendliness), acceptability (trust), comprehension, new information learned, and feedback from received messages was assessed by trained callers during phone calls at 5 to 6 months after delivery. We measured acceptability (proportion of participants who trust the messages), comprehension (proportion of participants who can describe the last message received), and new information learned (proportion of participants who indicate they learned new information about breastfeeding). These instruments have been widely used in mHealth evaluations in other countries [20,57-60] and took about 10 minutes to administer.

At completion, a qualitative study was conducted with intervention group participants. Based on information from follow-up calls, participants were split into 3 subgroups: EBF for 6 months, predominant and other types of breastfeeding (excluding EBF), and breastfed for less than 1 month only. In-depth interviews were held with approximately 25 women (7 to 9 women from each group) using semistructured guidelines. We explored user experiences in receiving SMS text messages, perceptions about the number of messages received, message delivery success, acceptance of the service delivery model, and effect of messages on breastfeeding practices. We expected that this number of participants would allow us to reach saturation point [60]. There were variations in the numbers of participants we could interview based on breastfeeding outcome, participant’s availability, logistic reasons, and feasibility of the study.

### Data Analysis

Quantitative data were collected via tablets and automatically submitted to the Dimagi server from which we could monitor data and generate reports. Stata software version 13 (StataCorp LLC) was used for data analyses. The intervention and control group outcomes will be compared using intention-to-treat principles [61]. Descriptive analyses were used to summarize participant baseline characteristics and breastfeeding practices. Likert scales were analyzed using Mann-Whitney U tests or cumulative odds ratios and proportions between groups using chi-square tests. Duration of EBF was compared by survival analyses with log-rank tests for between-group comparisons. If differences in baseline characteristics of the groups are identified, multivariable analyses will be undertaken. We report results using the CONSORT guidelines for reporting of randomized trials [62]. As follow-up data collection had to rely on the mothers’ self-reporting alone, we adjusted the potential social desirability bias [43] in our analyses to confirm the accuracy of self-reported outcome measures.

For process evaluation, we used Stata software for survey data analysis. We conducted descriptive analyses to summarize participant baseline characteristics and their experiences and feedback about receiving text messages. Text message delivery success was measured by the frequencies of messages received, and proportions were compared with chi-square tests. For the qualitative study, we used thematic analysis. All digitally recorded interviews were transcribed verbatim in Burmese in Microsoft Word and were reviewed to check for accuracy and translated to English. A list of thematic codes was developed by MPH, which was independently reviewed and verified by AA. The data were then be manually coded by MPH for emerging themes, which were again verified by other investigators and the most relevant themes are summarized in a document.

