**Methods:**

M528 is a 2-group parallel-arm randomized controlled trial with 9 months follow-up from recruitment until 6 months post-delivery. A total of 353 pregnant women between 28 and 34 weeks’ gestation who had access to a mobile phone and were able to read and write have been recruited from the Central Women’s Hospital, Yangon, and allocated randomly to an intervention or control group in a 1:1 ratio. The intervention group received breastfeeding promotional SMS messages 3 times a week while the control group received maternal and child health care messages (excluding breastfeeding-related messages) once a week. The SMS messages were tailored for the women’s stage of gestation or the child’s age. A formative qualitative study was conducted prior to the trial to inform the study design and text message content. We hypothesize that the exclusive breastfeeding rate in the intervention group will be double that in the control group. The primary outcome is exclusive breastfeeding from birth to 6 months and secondary outcomes are median durations of exclusive breastfeeding and other infant feeding practices. Both primary and secondary outcomes were assessed by monthly phone calls at 1 to 6 months postdelivery in both groups. Participants’ delivery status was tracked through text messages, phone calls, and hospital records, and delivery characteristics were assessed 1 month after delivery. Child morbidity and breastfeeding self-efficacy scores were assessed at 1, 3, and 5 months postdelivery. Social desirability was measured at 5 months, and text messages expressing delivery success and user experience were assessed at the end of the study.

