The objective of this study is to implement a mobile phone–based EBF promotion in pregnant women attending the antenatal clinic at Central Women’s Hospital, Yangon, and to evaluate its impact on breastfeeding practices. The primary hypothesis is to test whether breastfeeding promotional text messages can help increase EBF practices in the intervention group. We hypothesize that EBF rates in the intervention group during the 6 months after delivery will be double (30%) that of the control group (15%). Although the Myanmar Multiple Indicator Cluster Survey 2010 reported that 24% of infants younger than 6 months were exclusively breastfed, only 15% of infants were exclusively breastfed until they were 6 months old [4]. We, therefore, set the control group’s EBF rate at 15% and expect that the intervention group will have EBF rate at 30% at the end of the study. This is realistic as other intervention studies using text messages to promote EBF practices have reported a more than 2-fold increase in the odds of EBF. For example, a trial in China found a higher EBF rate at 6 months postdelivery in the intervention group (adjusted odd ratios [AOR] 2.58, 95% CI 1.4-3.7) [31] and a trial in Nigeria showed a similar result (AOR 2.40, 95% CI 1.4-4.0) [32]. Our secondary hypotheses are that receiving breastfeeding promotional text messages will result in higher appropriate infant feeding practices in the intervention group compared to that of the control group. We assessed women’s feeding practices, breastfeeding self-efficacy scales, and delivery and child morbidity characteristics during follow-up. We also conducted a process evaluation at the end of the study. Our findings will also help to provide recommendations on how mHealth-based breastfeeding promotion programs can be further improved for use in wider populations.

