### Sample Size Determination

Stata version 13.0 (StataCorp LLC) was used for sample size estimation and data analysis. Sample size was calculated with the assumptions of 80% power, 5% 2-sided alpha, and 13% expected loss at follow-up. The EBF rate of Myanmar children at 6 months of age was 15% [4], and we hypothesize that EBF in the intervention group will be increased 2-fold. The estimated sample size was 312 (156 per group) and the final sample size requirement was 353 participants to allow for 13% loss at follow-up.

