### Follow-Up Data Collection

Follow-up comprised a postdelivery survey, feeding follow-up assessments, morbidity, breastfeeding self-efficacy, and social desirability assessments. Questionnaires have been adopted from the Global Strategy for Infant and Young Child Feeding [6] indicators for assessing infant and young child feeding recommendations by WHO [38-40], breastfeeding efficacy scales [41,42], a short version of the Marlowe-Crowne Social Desirability Scale [43], and unpublished questionnaires being used in ongoing projects in Bangladesh (MJD and ML) and Indonesia (MJD).

The postdelivery form was completed when the child was 10 days old and was used to assess his or her postdelivery status, including the date, place, and type of delivery and the child’s birth weight, sex, and perinatal outcomes. The feeding follow-up form was completed every month and asked if the child was breastfed and if other liquids or foods were given in the last 24 hours and over the preceding month since the last contact (or birth for the first follow-up). Each participant completed 6 assessments of their feeding practices, including detailed information about the different types of liquids and foods (Textbox 1).

Child morbidity status and self-efficacy were assessed when the child was 1, 3, and 5 months of age using items from a validated instrument [7,41,42]. Child morbidity questions were used to record whether the child has had any signs or symptoms such as fever, cough, cold, running nose, rapid breathing, difficulty in breathing, chest indrawing, and diarrhea and dysentery. If one of these was present, we further explored the duration of illness. Breastfeeding self-efficacy was collected at 1, 3, and 5 months postdelivery to ascertain the mothers’ confidence to breastfeed, the relationship between self-efficacy and breastfeeding duration, and whether text messages improved breastfeeding self-efficacy. Studies report that women with a higher perceived self-efficacy for breastfeeding tend to initiate breastfeeding and persist even through challenges, and we hope that women in our study will increase their confidence or self-efficacy to continue EBF because of the knowledge gained from the text messages they received [41,42,44,45].

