### Outcome Measures

The primary outcome is the rate of EBF at 1 to 6 months of the infants’ age measured at monthly intervals after delivery. Secondary outcomes are median duration of EBF and rates of early initiation of breastfeeding (within 1 hour after birth); predominant breastfeeding; current breastfeeding; bottle feeding; and early introduction of solid, semisolid, or soft foods at 1 to 6 months of infant’s age (measured at monthly intervals) [38-40]. We used WHO infant and young child feeding definitions for this study, and definitions of these outcomes are described in Multimedia Appendix 1 [38].

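### Median EBF duration needs an interval-censored estimate: as described, the monthly calls locate the end of EBF only between two calls, and the plan names only standard survival analysis with a log-rank test

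*Protocol article*

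**What the plan says.** Under Outcome Measures, the protocol article puts median duration first among the secondary outcomes: "Secondary outcomes are median duration of EBF and rates of early initiation of breastfeeding".

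Under Follow-Up Data Collection, the feeding form is completed monthly and asks whether the child was breastfed and whether "other liquids or foods were given in the last 24 hours and over the preceding month since the last contact". Table 1 lists the same module as a 24-hour and a 1-month recall at each of months 1 to 6. No date or age at first introduction of other liquids or foods is described. For illness, by contrast, the same section says that duration was explored.

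Under Data Analysis, the only statement on duration is "Duration of EBF was compared by survival analyses with log-rank tests for between-group comparisons". The article gives no rule for the time assigned to the end of EBF and does not mention interval-censored data.

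**The concern.** A mother who reports only breast milk at the month 2 call and formula at the month 3 call stopped EBF somewhere in between. A Kaplan-Meier curve and its median need one time per woman. If that time is a call, the curve can drop only at calls, so the median can fall only at about 1, 2, 3, 4, 5 or 6 months.

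The median durations by group are likely to be quoted from the trial report. Under the plan's own assumptions the expected difference between them is a little over one month, about the same size as the step. Each median could be off by up to about a month, in a direction that depends on a convention the article does not state. The primary outcome, EBF rates at monthly intervals, is not affected.

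**Working it through.** **Inputs.** Control EBF at 6 months: "The EBF rate of Myanmar children at 6 months of age was 15" per cent (Sample Size Determination). Intervention: "expect that the intervention group will have EBF rate at 30% at the end of the study" (Introduction). Calls take place at months 1 to 6 on the same schedule in both groups. The article states no median, hazard ratio or event count for duration, so there is no planned figure to reproduce. The shape of the EBF curve is my assumption and is varied below.

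**Constant hazards.** With S(t) = exp(−ht):
- Control: h = −ln(0.15)/6 = 0.316 per month; median = ln 2/0.316 = 2.19 months.
- Intervention: h = −ln(0.30)/6 = 0.201 per month; median = ln 2/0.201 = 3.45 months.
- True difference: 3.45 − 2.19 = 1.26 months.

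S(t) at months 1 to 6 is 0.73, 0.53, 0.39, 0.28, 0.21, 0.15 (control) and 0.82, 0.67, 0.55, 0.45, 0.37, 0.30 (intervention). The curves cross 50% between months 2 and 3 and between months 3 and 4.

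| Cessation dated at | Control | Intervention | Error against truth |
|---|---|---|---|
| First call without EBF | 3 | 4 | +0.81, +0.55 |
| Last call with EBF | 2 | 3 | −0.19, −0.45 |
| Midpoint | 2.5 | 3.5 | +0.31, +0.05 |
| Linear interpolation within the interval | 2.22 | 3.48 | +0.03, +0.03 |

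The last row is 2 + (0.531 − 0.5)/(0.531 − 0.387) = 2.22 and 3 + (0.548 − 0.5)/(0.548 − 0.448) = 3.48.

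**Other curve shapes.** Weibull, S(t) = exp(−at^k), with a set so that S(6) is 0.15 or 0.30; median = (ln 2/a)^(1/k).

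| k | True medians | True difference | At first call without EBF | At last call with EBF |
|---|---|---|---|---|
| 0.6 | 1.12, 2.39 | 1.27 | 2, 3 | 1, 2 |
| 0.8 | 1.70, 3.01 | 1.30 | 2, 4 | 1, 3 |
| 1.0 | 2.19, 3.45 | 1.26 | 3, 4 | 2, 3 |
| 1.3 | 2.77, 3.92 | 1.16 | 3, 4 | 2, 3 |
| 1.6 | 3.20, 4.25 | 1.05 | 4, 5 | 3, 4 |

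The upward shift ranges from about 0.1 to 1.0 month and the downward shift from about 0.0 to 0.9. The true difference stays between 1.05 and 1.30 months, while the call-based difference is 1 or 2.

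**Sampling behaviour of the difference in medians.** The plan recruits 353 and allows for 13% loss: 353 × 0.87 = 307, about 153 per group. Simulated with constant hazards and complete calls:
- Dated at the first call without EBF, the medians average about 2.8 and 4.0. Their difference averages 1.20 with SD about 0.63 to 0.65 across runs; it is 0 in 9% of trials, 1 in 63%, 2 in 25% and 3 in 2%.
- Interpolated between calls, the difference averages about 1.27 with SD 0.47.
- With exact times, the large-sample standard error of each median is 1/(h√n): 1/(0.316 × √153) = 0.26 and 1/(0.201 × √153) = 0.40. Combined, √(0.26² + 0.40²) = 0.48.

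Interpolation therefore loses essentially nothing against exact times. Call dating raises the variance of the difference by a factor of (0.63/0.47)² = 1.8 to (0.65/0.47)² = 1.9.

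**Log-rank test** (156 per group, 1,500 runs, no dropout), month-grouped against exact times: type I error 5.1% against 4.9%; power 94.3% against 94.1% for 15% versus 30%, and 42.9% against 43.5% for 15% versus 22%. Grouping does not harm the test.

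**The case against.** The strongest reply is that the article never says cessation is treated as exact or dated at a call. Survival analyses can include interval-based medians, the form is not shown and might ask age at first introduction, and event-time rules are often left to a fuller document. This stands as far as it goes: the point is conditional on what the article describes. What remains is that the described form yields intervals, while the one method named is the usual one for observed or right-censored times.

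Four stronger readings are tempting but not supported:

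- **Both medians are too long.** This holds only if cessation is dated at the first call without EBF. Dating at the last call with EBF makes them too short.
- **The log-rank comparison is invalid.** It is not; both groups share one call schedule, and size and power are unchanged.
- **The between-group difference is mainly a product of rounding.** Its average, 1.20, is close to the true 1.26. Of the variance on the call grid (0.63² = 0.40), 0.48² = 0.23 would be present with exact times. Rounding adds noise but is not the larger part.
- **Missed calls will bias the comparison.** The article expects some unanswered calls but gives no rate and no reason for a difference between groups. Recall runs back to the last contact, so a missed call widens the interval without leaving a gap in the feeding history. The article also plans repeat calls and alternate numbers.

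It can also be said that durations could be computed from the recorded delivery date in days of age at the call. The steps would then be approximately, not exactly, whole months; the shift would remain.

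**Conclusion.** The concern holds in a limited form. If call times serve as event times, each median EBF duration moves in steps of about a month and is displaced by up to about one month, upward or downward according to an unstated convention. The difference in medians is nearly unbiased on average, but its SD is about 0.63 to 0.65 months against 0.47 for an estimate that uses the intervals. The log-rank test and the primary outcome are not at risk.

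The sizes rest on assumed curve shapes (constant hazard, or Weibull shapes 0.6 to 1.6) fixed to the plan's 15% and 30% at 6 months, with complete calls. The point falls away if the form recorded age at first introduction and that age is what is analysed. It is worth correcting because it concerns a named secondary outcome and the article reports that analysis is still under way, but no main conclusion turns on it.

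**What to change.** - Keep the log-rank test as the between-group test of duration.
- Code each woman's cessation as the interval from the last call with EBF to the first call without it. A missed call widens the interval; women still exclusively breastfeeding at their last call are right-censored there.
- Report the two medians and their confidence intervals from an interval-censored estimator, either nonparametric with a stated rule for placing the median within the interval, or parametric interval regression.
- If the form did record age at first introduction of other liquids or foods, state this and use that age.
- A hazard ratio from a discrete-time complementary log-log model is optional.

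The cost is a sentence in the analysis section, a little more code, and a mild assumption about what happens within a month. No new data are needed.

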### Baseline Data Collection

Baseline questionnaires comprised instruments which have been validated and tested for reliability and were adapted from the 2011 Myanmar Multiple Indicator Cluster Survey [4] 2015, Myanmar census questionnaires [36], the 2011 Demographic and Health Survey, Bangladesh [7], and a 2012 study from Shanghai, China [37]. At baseline, participants were asked to provide information on their socioeconomic status, previous pregnancies and breastfeeding history, knowledge and sources of breastfeeding information, confidence to breastfeed and perceived self-efficacy to breastfeed, intention to breastfeed, and intended breastfeeding patterns.

**Table 1 table1:** Summary of instruments used at various times in the M528 trial.

Instruments	Baseline	Postpartum month					
		1	2	3	4	5	6
Individual socioeconomic factors (participant and husband): age, sex, ethnicity, religion, education, occupation	x						
Household factors: income level, wealth index	x						
Previous pregnancy, childbirth and breastfeeding experience	x						
Breastfeeding knowledge level (high/medium/low)	x						
Intention and confidence to exclusively breastfeed	x						
Breastfeeding self-efficacy scores (high/low)	x	x		x		x	
Postdelivery survey: date of birth; place of birth; type of delivery; and child’s birth, weight, and sex		x					
Child morbidity characteristics: signs and symptoms of fever, cough, respiratory tract infection, diarrhea, dysentery		x		x		x	
Breastfeeding and other feeding follow-up module—24-hour recall and 1-month recall		x	x	x	x	x	x
Social desirability scale (high/medium/low)						x	
Process evaluation on mHealth (intervention group only): frequency of text messages received, user-friendliness of the messages received, perceived relevance of messages, trust in messages, understanding of messages, and new information learned or not							x

We will examine the relationship between breastfeeding duration and self-efficacy using self-report Likert scales (no confidence= 1, somewhat confident= 2, sometimes confident= 3, confident= 4, very confident= 5) [38,39]. With 5 levels of responses to 33 items, total scores range from 33 to 165 and will be categorized as low self-efficacy (1 to 82) and high self-efficacy (83 to 165).

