List of different types of liquids and foods.Liquids or fluids:Plain waterJuice or juice drinks, honeyOralit or any oral replacement therapy (ORS), including fruity ORS made in ChinaVitamin drops or other medicines as drops including traditional Burmese medicineInfant formula milk such as Nestle, Dumex, Chinese brands^a^, and Red CowMilk that is tinned or powdered (PEP, Red Cow) or fresh animal milk such as cow or goat milkClear broth or other soup, such as chicken, beef, or fish brothAny other water-based liquids such as sugar water, rice water, green tea, tea, coffee mix, or sodaSoya milk or yogurtSemisolid and solid foods:Branded baby food, such as SUN, Nestle, Dumex, Chinese brands^a^)Rice powder, cooked or blended rice, bread, noodles, porridge, or other foods made from grains such as sagoPumpkin, carrots, squash, or sweet potatoes that are yellow or orange insideWhite potatoes, yams, manioc, cassava, or any other foods made from rootsAny dark green leafy vegetables such as water cress, drum stick, lady finger, and spinachFruit rich in vitamin A such as ripe mango, papaya, jack fruit, oranges, and persimmonsAny other fruits or vegetables such as banana, guava, apples, green beans, and peasLiver, kidney, heart, or other organ meatsAny meat such as beef, pork, lamb, goat, chicken, or duckEggsFresh or dried fish, dried shrimp, or other seafood^a^Chinese brand milk products means imported milk products from the Myanmar-China border with or without registration.

We also assessed social desirability status, which is the tendency respondents have to answer questions in a way that is viewed favorably by others (such as research team members). This can interfere with the interpretation of average tendencies as well as individual differences [43]. By measuring social desirability status, we were able to assess whether follow-up data were influenced by bias. We used the validated and reliable short version of the Marlowe-Crowne Social Desirability Scale, which is based on a subset of 13 items adapted from Reynolds and Gerbasi [43].

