**Assessments**											
	Baseline survey	x									
	Delivery check by text and phone calls			x	x						
	Follow-up phone calls to assess										
	Postdelivery status					x					
	Feeding follow-up status					x	x	x	x	x	x
	Child morbidity and self-efficacy scale					x		x		x	
	Social desirability scale										x
	Evaluation on mHealth (intervention group): phone-based survey and qualitative study										x

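### Adjusting for a social desirability score taken only at month 5 or 6 cannot be relied on to confirm the accuracy of self-reported feeding, and could bias the randomized comparison

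*Protocol article*

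**What the plan says.** The Data Analysis section gives the reason for the adjustment, "As follow-up data collection had to rely on the mothers’ self-reporting alone", and then the step itself: "we adjusted the potential social desirability bias [43] in our analyses to confirm the accuracy of self-reported outcome measures". Follow-Up Data Collection describes the instrument as a "short version of the Marlowe-Crowne Social Desirability Scale, which is based on a subset of 13 items". It defines what is measured as "the tendency respondents have to answer questions in a way that is viewed favorably by others", and says that with it "we were able to assess whether follow-up data were influenced by bias".

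The timing is stated three times, and the statements do not agree:

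- Abstract, Methods: "Social desirability was measured at 5 months".
- Table 1: the row "Social desirability scale (high/medium/low" is marked at postpartum month 5 only.
- Table 2: the row "Social desirability scale" is marked at month 6 only.

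No place gives a baseline measurement. Data Analysis also names comparison by intention to treat, chi-square tests for proportions and log-rank tests for duration of exclusive breastfeeding (EBF). It does not say whether the score-adjusted analysis is primary or supportive, nor in what form the score enters.

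**The concern.** The reporting error that matters here is differential. Only the intervention arm receives breastfeeding messages, three times a week, and the Blinding section accepts that the intervention could not be blinded. Women repeatedly advised to breastfeed exclusively may over-report doing so more than controls, and that would look like a treatment effect.

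A general response-tendency score collected near the end of follow-up does not measure this. There are two broad possibilities. The score may be a stable trait, in which case randomization balances it and it has little to do with the arm contrast. Or it may be altered by months of messages, in which case it is a consequence of treatment. Neither gives adjustment the power to confirm that reports are accurate. The practical risk is false reassurance: an estimate that barely moves after adjustment would be taken as evidence that the self-reports are sound.

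**Working it through.** The plan gives no figure for this point, so there is none to reproduce. From the article come the EBF rates (15% control, 30% intervention, a difference of 15 points), 353 women and 13% expected loss. All misreporting rates and score effects below are assumptions chosen for illustration.

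**1. What adjustment can do.** In a linear risk-difference model with the score as a main effect,

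adjusted difference = crude difference − b × (mean score in intervention − mean score in control),

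where b is the within-arm slope of reported EBF on the score. If the mean scores are equal, adjusted equals crude, however much over-reporting there is. If they differ, the estimate moves by an amount that depends on why score and outcome are related, which the data do not reveal.

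**2. Balanced score, by hand.** Let true EBF be 15% in both arms and let a share h of each arm score high. Among high scorers who are not exclusively breastfeeding, o_I over-report in the intervention arm and o_C in the control arm. The spurious difference is h × 0.85 × (o_I − o_C):

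| h | o_I | o_C | Crude | Adjusted by stratum |
|---|---|---|---|---|
| 0.3 | 0.15 | 0.05 | 0.3 × 0.85 × 0.10 = 0.0255 | 0.0255 |
| 0.4 | 0.20 | 0.05 | 0.4 × 0.85 × 0.15 = 0.0510 | 0.0510 |
| 0.5 | 0.25 | 0.05 | 0.5 × 0.85 × 0.20 = 0.0850 | 0.0850 |

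The columns agree because h is the same in both arms. These 2.6 to 8.5 points are the assumed over-reporting itself. They exist with or without adjustment.

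**3. Simulation.** Each case has 1,000,000 records, no true effect, and a linear model with and without the score:

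| Case | Crude | Adjusted |
|---|---|---|
| A. 10% of non-EBF intervention mothers over-report, unrelated to the score | 0.0867 | 0.0867 |
| B. Intervention over-reporting rises with the score; score balanced | 0.0875 | 0.0875 |
| C0. No over-reporting; score and EBF share a cause; no shift by arm | 0.0003 | 0.0004 |
| C1. As C0, score shifted by 0.3 | −0.0007 | −0.0143 |
| C2. As C0, score shifted by 0.6 | 0.0005 | −0.0265 |
| D. Score shifted by 0.5, the only route to over-reporting, no shared cause | 0.0175 | 0.0003 |

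Case A agrees with hand calculation: control EBF there was 13.0%, and 0.10 × (1 − 0.130) = 0.087. C1 and C2 agree with step 1: the changes of −0.0136 and −0.0270, divided by the shifts 0.3 and 0.6, both give b of about 0.045. The sign in C follows from the assumed directions; a shift the other way would reverse it.

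**4. Reading the cases together.** Adjustment does nothing in A and B, harms in C1 and C2, and works in D. In both C and D the score differs by arm and the estimate moves on adjustment. The trial observes only reported EBF, so it cannot tell a harmful move from a corrective one.

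**5. How much over-reporting would matter.** If true EBF were 15% in both arms and controls reported accurately, the whole planned difference would arise if a proportion o_I = (0.30 − 0.15) / (1 − 0.15) = 0.176 of non-EBF intervention mothers reported EBF. This is the kind of statement a sensitivity analysis can make and covariate adjustment cannot.

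**6. Missing scores.** The primary outcome is assessed monthly from month 1, but the score arrives at month 5 or 6. If the adjusted model used complete cases, women lost earlier would leave it even for months in which they were observed. The ceiling is 0.13 × 353 = 45.9, about 46 women.

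**The case against.** The strongest reply is that the article never makes the adjusted analysis primary. Intention-to-treat comparison, chi-square and log-rank tests come first, and the social desirability sentence comes later, tied to checking self-report. It can fairly be read as a sensitivity check. The form of the model is also unstated; a three-level score would equally suit stratification or an interaction, and such detail commonly sits in a fuller document. This stands, and it limits the severity.

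Several stronger readings are tempting, and the documents do not support them:

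- *That adjustment can never remove the bias.* Case D is an exception.
- *That this is the plan's only safeguard.* Both arms receive messages, women are not told how the messages differ, telephone interviewers are blinded to group, and staff are blinded to aims and hypotheses. It is the only analytic safeguard named for self-report; the others reduce differential reporting without excluding it.
- *That adjustment will distort the result.* Distortion requires the arm to affect the score. The article describes a general tendency and does not suggest that text messages change it. With no shift (case C0), no bias arises.
- *That 2.6 to 8.5 points measure harm done by adjusting.* They measure assumed over-reporting that adjustment fails to remove.
- *That 46 women will be dropped.* The 13% is total expected loss, not loss before month 5; complete-case handling is not stated; and many women lost early would lack a month-6 outcome anyway.

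A low-score-stratum comparison is also no clean remedy, since it conditions on the same post-randomization score.

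What the reply does not answer is the stated inference. Whatever the model and whatever its rank, adjusting for this score does not confirm the accuracy of the reports.

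**Conclusion.** The concern holds at moderate severity. The article attaches to the adjustment a conclusion that it cannot be relied on to deliver, and leaves open whether the adjusted result is the main one. With a balanced score, the main-effect adjustment changes nothing (a spurious 8.7 points before and after in case A). With a score shifted by treatment and sharing a cause with EBF, it introduced about 1.4 to 2.7 points of bias, small beside the planned 15 but created by the analysis itself. These sizes rest wholly on assumed misreporting rates and score effects and, for the adjustment, on a main-effect model that the article does not specify; they show the mechanism and do not estimate what happened in this trial. The conflict between month 5 and month 6 needs no assumption: it is on the face of the abstract and the two tables.

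**What to change.** 1. State that the primary comparison is the intention-to-treat contrast without the social desirability score.
2. Report the distribution of the score by arm, with the number of women missing it.
3. Label any score-adjusted, arm-by-score or low-score-stratum result as exploratory, and say that it is interpretable only if the score is similar in both arms.
4. Add a sensitivity analysis over a range of assumed arm-specific over-reporting rates. With no under-reporting, the corrected proportion in an arm is (reported − o) / (1 − o). Report the rates at which the conclusion would change.
5. Drop the claim that adjustment confirms accuracy; say instead that the score describes response tendency in the sample.
6. Give one time point for the score in the abstract, Table 1 and Table 2.

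The article says that follow-up is complete and analysis is under way, so the report should state which of these analyses were added at this stage. The cost is some rewording and a little extra analysis. The score-based results will have low power and remain descriptive, and the sensitivity analysis shows how robust the result is without establishing the true misreporting rate.
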